#### Secondary outcome analysis

All-cause mortality at 6 h, 24 h, 30 days, and 90 days, the proportion of participants who receive 10 or more units of any blood components, and presence of coagulopathy will each be analysed separately using the same model that is described for the primary outcome.

Organ failure-free days and days in critical care and an acute care hospital will be reported as a median and IQR, by treatment arm and overall.

Units of each blood component received in the 24 h after randomisation will be summarised with a median and interquartile range and analysed using a negative binomial model, with adjustment for AAS.

Amount of millilitres (ml) of cell salvage at 24 h after randomisation and lactate, base excess, and pH level in first sample taken on arrival at acute care hospital will be analysed separately using a mixed linear regression model, with adjustment for AAS.

For each of the additional haemostatic agents, the number of participants who received each agent will be presented by trial arm and overall.

Thrombosis (arterial or venous thrombosis) up to 30 days after randomisation (or death or hospital discharge, whichever is first) and transfusion reactions/events relating to pre-hospital blood components which have been reported to SHOT (Serious Hazards of Transfusion) occurring in the first 14 days after randomisation will be summarised.

The economic evaluation will establish the resources required to provide the whole blood intervention, estimate intervention as compared to standard care costs, and conduct a full incremental cost-effectiveness analysis. Analyses will be undertaken against a primary perspective of the NHS/Social Care. Cost and outcome data will be synthesised to present incremental cost-effectiveness ratios for the primary outcome and cost per quality-adjusted life-year at 90 days. Multivariable regression analyses and bootstrapping will be employed, uncertainty will be explored, and cost-effectiveness acceptability curves will be presented. The internationally recognised CHEERs guidelines will be followed, and planned analyses will be described in a health economics analysis plan, which will be fully concordant with the SAP.

### Interim analyses {21b}

An interim analysis will be conducted after 400 participants, who did not experience traumatic cardiac arrest, have been randomised to inform early stopping of the trial in the case of strong evidence of harm or benefit.

A blinded analysis after the first 300 participants have been randomised and reached 24 h will allow us to reassess sample size requirements and recruitment rates, including estimating the underlying overall event rate, the dropout rates, and proportion of participants in traumatic cardiac arrest [25].

### Methods for additional analyses (e.g. subgroup analyses) {20b}

The primary outcome analysis will be replicated for four subgroups:Presence of a traumatic brain injury defined as Abbreviated Injury Scale head score 3 or aboveAdult vs paediatric (< 16 years)Blunt vs penetrating traumatic injuryInjury Severity Score: ≤ 15 vs 16–25 vs ≥ 26

The last two of these subgroups have been added to allow comparison to previous trials.

We are interested in how the following factors are associated with the primary outcome. However, as these factors occur after randomisation and are not baseline characteristics, they cannot be subgroup analyses. Instead, each factor will be presented by treatment arm for the primary outcome. Then, each factor will be separately fitted in the primary outcome model to assess if the factor is significantly associated with the primary outcome after the other risk adjustment and how it affects the treatment effect. For the age of whole blood, only those in the intervention arm will be included, and hence, the data will just be tabulated by level of the factor against the primary outcome, and the treatment effect will not be explored.Anaesthetised pre-hospital or notTransport time to hospital: ≤ 20 min vs > 20 minAge of whole blood: age of units of whole blood in days categorized into young (1–14 days) and old (> 14 days)

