### Outcomes {12}

The primary outcome is the proportion of participants who have died (all-cause mortality) or received massive transfusion in the first 24 h from randomisation. A participant is considered randomised and entered into the trial when the trial intervention box has been opened.

For the purposes of analysis, two units of whole blood will be counted as equivalent to four total units due to the volume difference between the intervention and control arm, the fact that two units of whole blood contain the equivalent of two units of plasma plus two units of packed RBCs, and for the massive transfusion part of the primary analysis, both arms will start will an equal baseline.

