#### Primary outcome

The primary outcome will be determined as the proportion of participants who have either died (from all causes) or received 10 or more units of blood components, within the 24 h from randomisation (a participant is considered randomised and entered into the trial when the trial intervention box has been opened). The following will be included in the blood component count: RBC, platelets, whole blood, thawed plasma (or LyoPlas), and cryoprecipitate. In this trial, for the purposes of analysis, two units of whole blood will be counted as equivalent to four total units due to the volume difference between the intervention and control arm, the fact that two units of whole blood contain the equivalent of two units of plasma plus two units of packed RBCs, and for the massive transfusion part of the primary analysis, both arms will start will an equal baseline. The composite outcome will be analysed using a mixed logistic regression model with adjustment for AAS, fitted as a random effect. A superiority hypothesis will be tested and the results from the adjusted analysis will be considered the primary analysis.

All analyses will be performed on a modified intention to treat basis, to exclude participants who experience a traumatic cardiac arrest, but will include all other randomised patients on whom a value of the response variable has been obtained, including those randomised in error and regardless of the participants’ adherence to the protocol. The data will be presented and analysed according to the arm to which the participant was randomised, regardless of whether they received the randomised intervention or not.

The primary outcome will be replicated per protocol, which will exclude participants who experience a traumatic cardiac arrest, those who experience a protocol deviation, were randomised in error or were withdrawn from the trial. The data will be presented and analysed according to the arm to which the participant was randomised.

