The choice of the comparator arm represents current pre-hospital transfusion practice in England. Therefore, the main differences between the intervention and standard care arms are the addition of platelets in WB, and the fact that the WB transfusion is logistically easier and faster to administer than component therapy. We are not aware of any trials that have assessed the addition of platelets to RBC and/or plasma resuscitation in the pre-hospital setting, thus making this trial unique. A sub-study of the PROPRR trial in the hospital setting suggested that trauma patients who received early platelets had an 11% reduction in 24 h and 30-day mortality [22]. In the case of WB, platelets are cold-stored (unlike routine platelets that are stored at room temperature), and in vitro data have shown that platelet count declines in the WB during storage; however, platelets become more activated [18, 24, 26]. Therefore, it could be argued that activated platelets could be more effective in promoting haemostasis and rapidly stopping bleeding, although this may be associated with increased thrombotic risks, all of which will be assessed in this trial.

Observational studies have suggested survival benefits with WB transfusion versus component therapy (mostly at 24 h), with only one study reporting mortality benefit at 30 days (odds ratio 2.19; 95% CI 1.01–4.76; *p* = 0.047) [16, 21, 23]. Three observational studies reported no difference in 30-day mortality (*n* = 830), while one study (*n* = 354) showed a 13% decrease in 30-day mortality with WB transfusion (*p* = 0.002) compared with component therapy [13]. This reported an 8% absolute difference in 24-h mortality between WB (4%) vs component therapy (12%); it also showed a higher proportion of patients receiving massive transfusion in the WB group compared to component therapy (89% vs 78%).

Although there is some evidence of benefit with the use of WB, there have been no prospective randomised trials exploring the clinical and cost effectiveness of pre-hospital administration of WB versus component therapy for bleeding trauma patients. The optimal pre-hospital transfusion strategy has yet to be established and transfusion practice varies across the country. Therefore, it is essential for patients, healthcare professionals, and blood services that the clinical and cost effectiveness of pre-hospital WB transfusion is evaluated in a large trial before its widespread implementation in routine practice.

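### Pre-hospital anaesthesia and transport time, which the plan says arise after randomisation, are to be fitted in the primary model and the change in the treatment effect read off

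*Protocol article*

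**What the plan says.** The section on additional analyses ({20b}) first lists four subgroups. It then turns to pre-hospital anaesthesia (yes or no), transport time to hospital (20 minutes or less against more than 20) and age of the whole blood. It gives the reason for treating these separately: "as these factors occur after randomisation and are not baseline characteristics, they cannot be subgroup analyses".

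Each factor is to be shown by arm for the primary outcome. After that, "each factor will be separately fitted in the primary outcome model to assess if the factor is significantly associated with the primary outcome", and this is to be judged "after the other risk adjustment and how it affects the treatment effect". Age of whole blood exists in one arm only, so there "the data will just be tabulated by level of the factor against the primary outcome, and the treatment effect will not be explored".

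Three other places matter:
- Outcomes {12} fixes the moment of randomisation: "A participant is considered randomised and entered into the trial when the trial intervention box has been opened".
- The primary outcome section fixes the model: "The composite outcome will be analysed using a mixed logistic regression model with adjustment for AAS, fitted as a random effect".
- The Discussion names, as one of the main differences between the arms, that "the WB transfusion is logistically easier and faster to administer than component therapy".

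**The concern.** The reason for refusing a subgroup analysis is that the factor may itself be a consequence of allocation. That reason applies equally to entering the factor as a covariate and comparing the treatment odds ratio with and without it. Both condition on something measured after randomisation. Moving the factors out of the subgroup list does not remove the difficulty.

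If arm influences the factor, and unmeasured severity influences both the factor and the outcome, then participants at the same level of the factor are no longer comparable between arms. The treatment odds ratio can then move away from its true value. A reader of the report would see it shift and could not tell this artefact from a genuine explanation of the effect, although that explanation is what the stated step sets out to read.

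**Working it through.** The section gives no figure for this analysis, so there is none to reproduce. The check has two parts.

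**1. Can arm influence the factors, on the document's own account?**
- Randomisation is the opening of the box (Outcomes {12}), and the article itself places the factors after it ({20b}).
- The crew is blinded only until the box is opened (Who will be blinded {17a}). Later pre-hospital decisions are made knowing the allocation.
- Whole blood is described as faster to administer (Discussion).
- The primary model adjusts for air ambulance service only, so severity stays unadjusted.

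An effect of arm on either factor is therefore plausible. No place in the article states or quantifies one.

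**2. What would happen if it did?** The set-up below is an assumption throughout, apart from the event rate, which is chosen to lie close to the plan's 68%.
- T is arm (0 control, 1 whole blood), randomised 1:1. U is unmeasured severity, standard normal.
- Factor M: P(M = 1) = expit(g·U + d·T).
- Outcome Y: P(Y = 1) = expit(0.9 + 1.2·U). T is absent, so the true odds ratio is 1.00. The overall event rate is about 67%.
- Fit logistic Y on T, then Y on T and M.

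| Dependence on severity, g | Arm effect, d | Factor, control to whole blood | Adjusted OR for T |
|---|---|---|---|
| 1 | 0 | 50% to 50% | no change from unadjusted |
| 1 | −0.5 | 50% to 40% | 1.08 to 1.09 |
| 1 | −1 | 50% to 30% | 1.17 |
| 2 | −1 | 50% to 35% | 1.20 to 1.21 |

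Where two values are given, they come from separate simulation runs of one to two million participants and differ only by simulation error. The unadjusted odds ratio is 1.00 within the same error.

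The second row can be followed by hand. Integrating over U gives these event rates:
- Factor absent: 58.1% control, 60.0% whole blood. OR = (0.600/0.400)/(0.581/0.419) = 1.08.
- Factor present: 75.7% control, 77.3% whole blood. OR = (0.773/0.227)/(0.757/0.243) = 1.09.
- Overall, control: 0.50 × 58.1 + 0.50 × 75.7 = 66.9%.
- Overall, whole blood: 0.602 × 60.0 + 0.398 × 77.3 = 66.9%.

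The arms are identical overall, yet whole blood looks worse at each level of the factor. Fewer whole-blood participants have the factor, so those without it include more severe cases, and those who still have it are more severe too.

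Weaker assumptions give less. With a log odds ratio of 1 per SD of severity on both factor and outcome, shifts of the factor by odds ratios of 0.78, 0.61 and 0.37 give adjusted odds ratios of about 1.03, 1.07 and 1.16. With no shift, the odds ratio is 1.007 before adjustment and 1.008 after.

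The illustration has no path from M to Y. It shows the distortion through severity only and does not measure any loss of benefit that might run through the factor.

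**The case against.** The case against has real force. This is an additional analysis, and the stated interest is in how the factors relate to the outcome. The authors decline to call these subgroups, show each factor by arm first, and keep age of whole blood out of the model. Faster administration is not the same as a different transport time or a different need for anaesthesia. The article lets the transfusion continue after arrival ({11a}, {11b}), so a quicker product need not change the journey. No figure supports any arm effect on either factor, and without one the illustration shows no distortion.

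These points limit the size and weight of the matter. They do not remove it, because the plan states a second purpose, reading the change in the treatment effect, and that reading is sound only if arm leaves the factor alone.

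A reader might also infer two stronger things that the document does not support:
- **That participants who die before transport fall out of the model.** The article gives no rule for a missing transport time and may leave it to the analysis plan. The issue could concern transport time only, because anaesthesia status exists for everyone. Such deaths may also be largely outside the analysis set already: "All analyses will be performed on a modified intention to treat basis, to exclude participants who experience a traumatic cardiac arrest".
- **That the adjusted estimate has no causal meaning at all.** That is too absolute. It fails as a treatment effect if the factor depends on arm, and that dependence is plausible but not shown.

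**Conclusion.** The point holds in a limited form. The plan states an analysis that conditions on two factors it acknowledges to be post-randomisation and interprets the resulting change in the treatment odds ratio. That interpretation is not safe unless the factor is unaffected by arm.

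The possible size is hypothetical: an adjusted odds ratio of about 1.08 to 1.21 under a true null, if whole blood lowers the factor from 50% to between 40% and 30% and severity drives both factor and outcome, and no change if treatment does not move the factor. Both the shift and the strength of the severity link are assumptions.

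The primary analysis, the sample size and the type I error are unaffected. What is at stake is how the trial's main result might be reinterpreted through these secondary models.

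**What to change.** In {20b}, and in the analysis plan:
- Keep the tabulation of pre-hospital anaesthesia and transport time by arm against the primary outcome, in line with the tabulation already chosen for age of whole blood.
- Delete the step that examines how each factor affects the treatment effect.
- If the model is kept to describe association with outcome, report only the factor's own association, label it exploratory, and do not interpret the change in the treatment odds ratio.
- If effect modification is of interest, use a treatment-by-factor interaction on versions of the factors fixed at box opening, but only if those data are already collected. The data listed in {18a} name no such items, and recruitment opened on 15 December 2022, so new collection should not be started for this purpose alone.

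The cost is a change of wording and the loss of one exploratory adjusted estimate for each of the two factors.

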### Methods in analysis to handle protocol non-adherence and any statistical methods to handle missing data {20c}

Protocol deviations will be monitored throughout the trial and will be assessed as minor or major and whether they influence the statistical analysis. For the primary analysis, any missing data for the primary and secondary outcome measures will be treated as missing data and not be imputed. If an outcome has data missing for more than 25% of participants, then the analysis will not be undertaken. All missing primary and secondary outcome data will be summarised.

A sensitivity analysis will be conducted if the primary outcome is missing for more than 5% of participants, which will impute the composite endpoint.

### Plans to give access to the full protocol, participant-level data, and statistical code {31c}

The full trial protocol is available on request. The final dataset will reside with NHSBT. Access to the final dataset for additional analyses will be permitted under the agreement of the trial review committee (made up of the sponsor representative, chief investigators, trial statistician, and NHSBT information governance) and according to the trial publication policy.

## Oversight and monitoring

### Composition of the coordinating centre and trial steering committee {5d}

The trial will be managed by the NHSBT Clinical Trials Unit, with day-to-day input from a trial manager, trial coordinator, and clinical operations manager. A trial management group (TMG), made up of the two chief investigators, co-applicants, trial statisticians, and trial managers, will meet every 2 weeks during the trial set-up phase, and monthly thereafter, to monitor trial conduct, safety, recruitment, and follow-up.

An independent trial steering committee (TSC) has been convened with an independent chair, independent members with relevant clinical experience, and patient and lay representatives. The role of the TSC is to safeguard the well-being of patients and monitor overall conduct of this trial, e.g. organisation and implementation of the trial protocol. It should also provide advice through its independent chair to the trial management group (TMG), trial sponsor, and the CTU on all aspects of the trial. The TSC will be responsible for making executive decisions about the trial, considering advice and recommendations provided by the data monitoring committee (DMC).

### Composition of the data monitoring committee, its role and reporting structure {21a}

An independent data monitoring committee (DMC) has been convened with an independent chair and independent statistician. The DMC members will be the only individuals, along with the trial statisticians, to see outcome data by arm and overall while the trial is ongoing. It will review the trial progress and data management and make recommendations to the TSC and TMG. The DMC charter is stored in the Trial Master File at the CTU.

### Adverse event reporting and harms {22}

SWiFT trial participants have suffered traumatic injury and by definition will have multiple (serious) adverse events during their transfer to hospital and admission (related to their traumatic injury). Most of the AEs occurring in SWiFT, whether serious or not, will therefore be anticipated in the sense that they are recognised and accepted complications/consequences of major trauma.

All serious adverse events/reactions which relate to the administration of the pre-hospital WB, standard of care components (RBC and FFP), or LyoPlas will be reported as serious adverse events.

Any unused units will be disposed of in accordance with local requirements. For used products, all hospital transfusion laboratories are required by BSQR to keep the evidence of traceability for every unit used (or wasted) for 30 years. The following data items will be electronically recorded: donation number, component type, blood establishment which provided the blood component, date provided, identity of patient who received the blood component, or final fate if not transfused. Furthermore, transfusion laboratories have SOPs in place that accurately report any serious adverse events or reactions relating to blood transfusion to national haemovigilance systems (SHOT).

### Frequency and plans for auditing trial conduct {23}

The frequency, type, and intensity for routine monitoring and the requirements for “for cause” monitoring is detailed in the trial monitoring plan. The intensity of the monitoring according to the risk assessment is moderate (i.e. 1 visit/call per annum).

Most data can be monitored centrally to support trial and data integrity, safeguard patient safety, and monitor primary study endpoints. Therefore, one monitoring visit/call per year will be carried out via telephone or video conferencing, and key data points will be monitored centrally on a bimonthly basis.

In addition to potential Good Clinical Practice (GCP) inspections or audits by the host R&D department, the sponsor and NHSBT CTU reserve the right to conduct site audits, either as part of its ongoing audit programme or in response to adverse observations.

### Plans for communicating important protocol amendments to relevant parties (e.g. trial participants, ethical committees) {25}

Any amendments to the approved protocol will be communicated to all relevant parties in an expedited manner by the CTU via email.

### Dissemination plans {31a}

On completion of the trial, the data will be analysed and tabulated, and a final trial report prepared. The main trial results will be presented at national and international conferences and published in a peer-reviewed journal, on behalf of all collaborators. All presentations and publications related to the trial will be authorised by the TMG, and responsibility for all trial publications will rest with the TMG. The final report’s abstract and references will be made accessible, and participants will be able to access the results through the SWiFT trial website.

